## Trial intervention

The trial intervention is prescription of 5000 ppm fluoride toothpaste, used as prescribed by the participant’s GDP and informed by national guidance [12]. The intervention is designed to reflect current dental practise and therefore the frequency of prescription, the number of tubes of toothpaste per prescription and the duration of the regimen will be determined by the patient’s GDPs after assessing each patient’s risk. We have restricted the intervention to 5000 ppm fluoride toothpaste, as NHS prescribing data shows that 5000 ppm is more commonly prescribed than the 2800 ppm alternative [17].

Current guidance recommends that for those adults with obvious *active* coronal or root caries dentists should prescribe high fluoride toothpaste [12]. Our inclusion criteria are less restrictive to allow for prescription based not just on caries activity, but also based on other risk factors, as determined by the GDP. This approach is based on the hypothesis that 5000 ppm fluoride toothpaste can prevent caries in those patients deemed to be high risk by their dentist, even though they don’t present with ‘obvious’ caries. For true primary prevention, the identification of risk factors in advance of disease is indicated.

The Investigational Medicinal Product (5000 ppm fluoride toothpaste) prescribed will not be specified by manufacturer or individual product. A clinical trials pharmacy will not be used to dispense the drug. The drug will be used as prescribed by the participant’s GDP and as indicated by the British National Formulary. Participants will be expected to collect their prescriptions at a local community pharmacy as per usual practice. GDPs will provide instructions to each participant based on their assessment of risk and how they prescribe the drug.

Compliance will depend on both GDPs’ and participants’ behaviour, the trial will not seek to ensure a minimal level of compliance. Compliance will be assessed to determine its impact on trial outcomes by recording GDPs’ self-reported prescribing behaviour frequency and duration of prescriptions and the number of tubes prescribed, accessing national datasets to identify if participants’ re-deem prescriptions or receive prescriptions from other sources and via participants’ (both test and control groups) self-reported use of toothpaste.

The comparator will be usual care; usually advice given by the participant’s GDP to buy ‘standard’, off-the-shelf 1350-1500 ppm fluoride toothpaste and use as advised by their dentist informed by national guidance [12]. Other recommendations in the national guidance [12] for self-administered (mouthwash) or professionally-applied (varnish) fluoride delivery methods could have an impact on the trial. We will take a pragmatic approach and leave the decision to use other fluoride delivery systems to the patients and their dentist, but the use of these interventions will be recorded.

## Outcome measures

### Primary outcome

The proportion of participants receiving any dental treatment due to caries; including restorations, endodontics or extraction. Any dental treatment provided and the reasons for providing treatment (caries, tooth wear or other e.g. trauma) will be recorded. The primary outcome (treatment directly due to caries) will be extracted from the Clinical Report Form (CRF).

### Secondary outcomes (clinically assessed)

The clinically assessed secondary outcomes will be measured in Scottish practices only; Additional file 3: Appendix 3 provides a sub-protocol for this more intensive assessment of participantsCoronal caries increment, including dentist replacement restorations for caries, at tooth surface (DMFS) level by independent, trained and calibrated, clinical examiners at baseline and 3 year (+/− 3 months) follow-up. We will use the ICDAS method [18] to assess caries as it provides flexibility to analyse and present caries data at different diagnostic thresholds.Root caries increment, including dentist replacement restorations for caries, at tooth surface (DMFRS) level by independent, clinical examiners at baseline and 3 year (+/− 3 months) follow-up.Early caries lesion progression data, using ICDAS.Bleeding on probing (BoP) will also be recorded by the independent clinical examiners. BoP provides evidence of long term optimal brushing rather than transitory measures such as visible plaque scores [19].

### Secondary outcomes (patient reported)

Oral health status using OHIP14, a measure of oral health-related Quality of Life (QoL), collected at baseline and annual follow up through patient administered questionnaires. The OHIP-14 is the most common, validated dental quality of life instrument and has been successfully used in previous HTA trials. It has been found to be sensitive to differences in oral health and is closely correlated with self-reported oral health outcomes [20]The EQ-5D-5 L profile measure of generic health status [21, 22], will be collected at baseline and annual follow up through patient questionnaires.Any episode of dental pain (and total number per participant) during the 3 year follow up period, severe enough to trigger seeking advice from a healthcare professional (dentist, GP, community pharmacist). This will be recorded at scheduled and unscheduled dental visits by patient questionnaire included in the CRF.Oral health behaviour, including self-reported brushing/other sources of fluoride. Evaluated at baseline and through annual questionnaires sent by mail to the home address of participants.

### Routine data

Fulfilment of prescriptions will be measured via Business Services Authority (BSA), Business Services Organisation (BSO) and Information Services Division (ISD) datasets. Adherence to the allocated intervention (prescription of 5000 ppm) will also be explored by dentist and participant self-reporting (via CRF) and in the qualitative interviews with patients

### Economic outcomes

Provision of NHS and privately-funded dental treatments will be collected from the CRF. In addition we will also collect information on NHS treatment completed using routinely collected NHS data held by the ISD, BSA and BSO. Treatment cost data will be collected for participants from 1 year prior to randomisation until the end of the trial.All remaining resource use data will be collected using questionnaires provided to participants on attendance for dental care or mailed to participants who fail to attend. These will include the use of other NHS healthcare services (e.g. GP visits, dental hospital attendances and other healthcare resource use) directly related to dental problems as well as data on non-NHS costs (e.g. time and travel costs, time off work, privately purchased care, self-purchased dental care products).Collection of EQ-5D-5 L will enable the calculation of the mean cost per additional QALY as a secondary health economic outcome.A discrete choice experiment (DCE) with an online representative sample of the UK general population (aged 50 and over) will be undertaken to elicit willingness to pay (WTP) for high fluoride toothpaste and associated patient relevant outcomesLong term economic evaluation with trial results extrapolated over a life-time horizon using Markov modelling methods

The methods used to collect the various outcome measures are summarised in Table 1.

**Table 1 Tab1:** Summary of methods used to collect outcome measures

	Baseline	Elective and non-elective visits to the dentist over 3 year follow up^a^	36 months	Annual Questionnaire	National Database
Clinical Status (full dental chart)	○	○	○		
Treatment details Check ups, restorations, endodontics, extractions (reason for treatment in CRF and all NHS treatments in national datasets) Prescription of toothpaste (date and amount prescribed) Relevant medical history and medication	○	○			X
Healthcare costs GDP completed CRF: payment mechanism (NHS/private) and charges levied Dental treatment received in other settings (patient element of CRF) NHS costs from national data sets Non NHS treatment costs in patient element of CRF)	○	○	○		X
Detailed independent clinical assessment ICDAS, BoP (Scotland only)	○		○		
EQ-5D-5 L	○			●	
OHIP-14	○			●	
Pain - seeking professional care because of pain	○	○			
Oral health behaviour	○			●	
Redemption of toothpaste prescriptions	○	○	○		X
Adverse reactions		○			

^a^dentists should invite participants to attend practice at least once a year

○ Dental Practice – CRF (includes both GDP and participant completed elements)

● Postal Questionnaire

X NHS centralised dental databases

## Follow up of participants

Participants will be followed up for a 3-year period. Participants will remain in the trial unless they choose to withdraw consent or if they are unable to continue for clinical reasons. All changes in status with the exception of complete withdrawal of consent will mean the participant is still followed up for all trial outcomes wherever possible. Participants randomised to 5000 ppm fluoride toothpaste, who for whatever reason, stop using the trial medication or participants randomised to routine care but who purchase or otherwise receive high fluoride toothpaste will not be considered to have withdrawn from the trial.

The Sponsor and CI have undertaken an initial risk assessment, which will be periodically reviewed and if necessary updated as the trial progresses. The Sponsor has concluded that this is a low risk trial, as the drug is being prescribed by GDPs as per its licensed indications. It is topically administered and the known side effects are rare and minor in nature [23].

Any Serious Adverse Reactions (SARs) will be recorded from the time a participant consents to join the study until the end of their follow up. The local investigator (GDP) will record in the CRF all directly observed Adverse Reactions (ARs) and all ARs spontaneously reported by participants that have a possible causal link to the IMP. In addition, each trial participant will be asked to complete a questionnaire at each attendance at their dental practice, and one sent annually to their home, which collects information on potential ARs and SARs.

The Sponsor and CI will ensure, through the independent Trial Steering Committee, that adequate systems are in place for monitoring the quality of the trial (compliance with appropriate governance) and appropriate expedited and routine reports, to a level appropriate to the risk assessment of the trial.

## Randomisation

Randomisation will be at patient level. Eligible and consenting participants will be randomised to intervention and control groups using a web-based application, hosted by the Clinical Trials Unit (CTU) CHaRT (Centre for Healthcare and Randomised Trials). The Principal Investigator (PI), or individual at site with delegated authority, will access the web-based system to randomise participants. The randomisation algorithm will use recruitment site, residential setting (own home/care home), exemption from dental treatment charges (yes/no) and age (50–65 years/over 65 years) as minimisation covariates to allocate treatment to intervention and control groups in a 1:1 ratio. A random element will be incorporated into the randomisation algorithm. Participants will be informed of their allocated treatment group following randomisation. The trial statistician and the study team will be blinded to the allocation during all analyses by use of a code to identify the two groups. The key to the code will be held by the CTU.

Blinding of outcome assessment using the primary outcome will not be possible, as the participant’s dentist will collect primary outcome data. A more detailed clinical examination undertaken by independent (external to the trial dental practices) examiners will be used to repeat primary outcome measures and collect secondary outcomes (coronal and root caries increments and bleeding on probing). This more detailed clinical examination will take place in Scottish practices only and the independent examiners will be blind to the allocation. Source data verification will be undertaken according to the monitoring plan by:Comparing the primary outcome measures with outcomes recorded in the clinical examination (Scotland only)Comparing primary outcome measure in the CRF treatment provided for caries (coronal and root surfaces) including restoration, extraction and endodontics with centralised NHS treatment claims data for individual patients.Source data verification audits in annual visits of each practice.

## Sample size considerations

The sample size calculation is based on a meaningful absolute target difference of 10% (75% vs 65%) in the primary outcome measure. This difference is considered to be both a realistic and important difference from discussion with dentists, PPI groups and from published estimates [6, 7]. The value for the comparator group (75% of individuals allocated to standard care who have restoration(s) or extraction(s) due to caries during the 36 months of follow up) is based on published data and Scottish treatment data [24]. For the proposed target difference, a two-sided 5% significance level, and 90% power, 440 participants (880 in total) will be required to provide data for the primary outcome at 36 months. Based on our previous and current HTA trials, we are assuming 25% attrition, and so 587 participants per group are required (1174 in total) in approximately 60 practices (each practice recruiting an average of 20 participants). Based on an estimated consent rate of 50% [data from IQuad [25]], 2348 eligible patients will be invited to participate.

An important secondary outcome within our proposed trial is caries increment, measured using the number of Decayed Missing and Filled tooth Surfaces (DMFS). Using the mean number of Decayed Missing and Filled tooth Surfaces (DMFS), the caries increments for an older population in the published literature vary, but there seems to be consensus around one surface per year [26]. Given the fact that the standard deviations approximate the means in terms of caries increment, a reduction in caries increment from 3 to 2 surfaces with the intervention would produce a ~ 30% reduction in caries increment with the intervention over 3 years. The numbers needed to adequately power this secondary outcome are relatively small compared with the primary outcome measure:

For secondary caries outcomes (Scotland only), group sample sizes of 200 and 200 achieve 97.5% power to reject the null hypothesis of equal means when the population mean difference DMFS increment is μ1 - μ2 = 2–3 = − 1.0 with standard deviations of 2 for group 1 (intervention) and 3 for group 2 (control), and with a significance level (alpha) of 0.05 using a two-sided two-sample t-test allowing for unequal variances. Assuming 25% attrition, 267 participants per group are required (534) in total in 28 practices. Based on an estimated consent rate of 50% 1068 eligible patients will be invited to participate.

## Statistical analysis

Statistical analysis will be conducted according to a detailed statistical analyses plan (SAP) which will include, but not be limited to the investigational plan and study design, listing of outcomes and final analysis including effectiveness evaluations. The SAP will set out the summary measures to be reported; methods of analysis, plans for handling missing data, non-compliance and withdrawals, the timing and frequency of analyses, and use of intention to treat analysis.

Demographic (age, sex) and baseline characteristics (DMFT, DMFS, concomitant illness / treatment, exempt\not exempt from NHS dental charges) will be summarised and displayed in tables for all randomised patients. In addition, mean NHS treatment costs in the 12 months prior to recruitment will be included in the baseline characteristics tables. Frequency counts and percentages will be used to present categorical data. Number of patients, mean, mode, median, SD, minimum, maximum and IQR will be used, as appropriate, to present continuous data.

The primary outcome measure will be analysed using a generalised linear model with the appropriate link function adjusting for the minimisation variables (recruitment site, residential setting, exemption (including partial exemption) from dental treatment charges and age band). Secondary outcomes will be analysed using generalised linear models with adjustment for minimisation and baseline variables when available. Statistical significance will be at the 2-sided 5% level with corresponding confidence intervals derived. Subgroup analyses on the primary outcome will explore the possible modification of treatment effect by clinically important factors; gender, age and NHS dental charges exemption status. This will be done by including treatment-by-factor interactions in the model and they will be classified as exploratory analyses. All analyses will initially be performed on an intention to treat basis, although we will consider additional analysis groups such as per-protocol for investigation of adverse events.

Outcome data will not be imputed for the primary analysis, but score data for participants who have not returned a scheduled questionnaire will be estimated using a multiple imputation approach to make use of partial outcome data. Sensitivity analyses will be conducted to assess the robustness of the treatment effect estimate to these approaches. Missing items on the health-related outcome measures will be treated as per the instructions for that particular measure. There are no planned interim outcome analyses; all analyses will occur following completion of trial follow up. Interim analyses will be performed only if requested by the Independent Data Monitoring Committee

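### The primary model leaves out baseline caries experience, which is already collected: a modest gain in precision is forgone

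*Protocol article*

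**What the plan says.** Under Statistical analysis, the protocol article fixes the adjustment set for the primary outcome: "The primary outcome measure will be analysed using a generalised linear model with the appropriate link function adjusting for the minimisation variables". It names them in brackets as recruitment site, residential setting, exemption from dental charges (including partial exemption) and age band. The same four appear under Randomisation: "The randomisation algorithm will use recruitment site, residential setting (own home/care home), exemption from dental treatment charges (yes/no) and age" in two bands. For the other outcomes the next sentence goes further: "Secondary outcomes will be analysed using generalised linear models with adjustment for minimisation and baseline variables when available".

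Three other places bear on the point:

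- **Baseline chart.** Table 1 (under Economic outcomes) has a row beginning "Clinical Status (full dental chart", marked at baseline and collected on the practice CRF.
- **Baseline tables.** Statistical analysis lists DMFT and DMFS among the characteristics to be tabulated for all randomised patients, together with mean NHS treatment cost in the 12 months before recruitment.
- **Eligibility.** Study participants admits people with active caries into dentine in the past year (treated or not), people with any root caries, and people with other risk factors judged by the dentist. Trial intervention explains that this is meant to include patients who do not show obvious caries.

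**The concern.** The primary outcome is any treatment for caries over three years. Someone who enters with untreated decay or a heavily restored mouth may well have a different chance of that outcome from someone enrolled on risk factors alone. Study participants itself says that heavily restored dentitions raise caries risk. Baseline caries is neither a minimisation factor nor a term in the primary model, so whatever prognostic information it holds is shown in a baseline table and not used in the main comparison.

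What is at stake is precision. A covariate that predicts the outcome reduces the variance of the estimated treatment effect and takes account of chance differences between the groups on that covariate. Here the covariate comes from data that the trial already plans to collect.

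**Working it through.** **1. The plan's own figure.** Inputs from Sample size considerations: a "meaningful absolute target difference of 10% (75% vs 65%) in the primary outcome measure", with "a two-sided 5% significance level, and 90% power". With pooled variance under the null and no continuity correction:

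n per group = [z(0.975) × √(2 × 0.70 × 0.30) + z(0.90) × √(0.75 × 0.25 + 0.65 × 0.35)]² / 0.10²

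= [1.960 × 0.6481 + 1.2816 × 0.6442]² / 0.01 = (1.2702 + 0.8256)² / 0.01 = 439.2, rounded up to 440.

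This matches the plan: "440 participants (880 in total) will be required to provide data for the primary outcome at 36 months". Attrition of 25% gives 440 / 0.75 = 586.7, rounded up to 587 per group, also as stated. Power at 440 per group is 90.0%. The calculation uses raw proportions and claims nothing from covariates.

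**2. Effect of one added covariate.** If the covariate explains a fraction R² of the outcome variance, the variance of the risk difference shrinks by about (1 − R²). The effective sample size per group is then 440 / (1 − R²), and the number needed for 90% power is 440 × (1 − R²). The article gives no R², so a range is assumed.

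| Assumed R² | Effective n per group | Power | n per group for 90% |
|---|---|---|---|
| 0 | 440 | 90.0% | 440 |
| 0.02 | 449 | 90.6% | 432 |
| 0.05 | 463 | 91.4% | 418 |
| 0.10 | 489 | 92.8% | 396 |
| 0.15 | 518 | 94.1% | 374 |
| 0.20 | 550 | 95.2% | 352 |

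From the rounded powers, the gain is 0.6 points at R² = 0.02, 2.8 at 0.10 and 5.2 at 0.20.

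**3. Check by simulation, continuous covariate.** 880 participants, marginal rates of 75% and 65%, a standard-normal covariate, logistic Wald test, 4,000 trials per row. The simulation standard error of each power is about √(0.9 × 0.1 / 4000) = 0.5 points.

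| Odds ratio per SD (assumed) | R² | Without covariate | With covariate |
|---|---|---|---|
| 1.25 | 0.01 | 90.9% | 90.9% |
| 1.5 | 0.03 | 89.1% | 90.1% |
| 2 | 0.09 | 90.3% | 92.7% |
| 2.5 | 0.14 | 89.0% | 92.9% |
| 3 | 0.18 | 91.6% | 95.3% |

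**4. Check by simulation, binary covariate.** With 50% prevalence and 8,000 trials per value, power moves from 90.0% to 90.4% at an odds ratio of 2, from 90.1% to 91.5% at 3, from 89.8% to 92.9% at 5, and from 89.9% to 94.7% at 8.

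Both simulations agree with step 2: almost nothing for a weak predictor and about 4 to 5 points for a strong one. Both compare a model with the covariate against a model with no covariates at all. The protocol's model already contains four adjusters, and their overlap with caries experience was not simulated. The gains are therefore an upper guide.

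**The case against.** The strongest reply is that nothing here is wrong. Adjusting for the factors used in the allocation is valid and matches the design, and the stated power is met. Statistical analysis refers methods to a separate SAP, which is not shown and may add covariates. Participants are all judged high risk, which may narrow the spread of prognosis and weaken any baseline predictor. All of this stands. What remains is that the article itself names a specific adjustment set, without a caries measure, when one is available.

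Several stronger readings are tempting, and the documents do not support them:

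- **The trial loses power against its plan.** It does not; the 90% was computed without covariates.
- **The effect estimate is biased.** Omitting a prognostic covariate makes the marginal odds ratio lie closer to 1 than the conditional one. That is non-collapsibility, not bias, and it does not affect a marginal risk difference. The test and interval already allow for chance imbalance.
- **The plan contradicts itself by adjusting secondary outcomes for baseline.** Baseline variables there can be read as the outcome's own starting value, which OHIP-14, EQ-5D-5L and the ICDAS measures have. Treatment during follow-up has no such counterpart.
- **Baseline caries and prior treatment are the strongest predictors.** The article reports no association with the 36-month outcome.
- **Eligibility route and prior caries treatment are ready to use.** The article does not say that the route is recorded, and its categories overlap. The prior-year data are described as treatment cost, not treatment for caries. NHS cost may be incomplete because patients may receive only part of their care on the NHS.
- **Age should be continuous.** The age band is the minimisation factor, and no gain from changing it has been shown.

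**Conclusion.** The point holds as a minor efficiency matter. The primary model has no measure of caries, although one is planned for everyone randomised and the entry criteria deliberately vary on it. The forgone gain is about 0.6 to 2.8 power points if the covariate explains 2% to 10% of outcome variance, and about 5 points at 20%. In participants, that is roughly 2% to 10%, and at most 20%, fewer evaluable people for the same power.

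This rests on three assumptions: the prognostic strength, which the article does not give; little overlap with site, residential setting, exemption and age band; and a baseline chart that is nearly complete. The sample size and the validity of the primary analysis are not in question.

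**What to change.** Before unblinding, prespecify one measure of caries experience from the baseline chart, for example DMFS or the number of untreated decayed surfaces, as an additional covariate in the primary model. Keep all four minimisation variables as they are. Take the measure from the practice chart, which covers all participants, and not from the independent examination, which is done in Scotland only. Report the treatment effect as a standardised risk difference, so that it can be read directly against the 10-point target.

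Add prior-year NHS treatment cost only if a check, made without reference to outcomes by group, shows it to be complete. Do not add eligibility route, and leave age in its bands.

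If the SAP already includes such a covariate, aligning the protocol wording is enough. Otherwise the cost is a sentence or two of analysis text, with no new data collection for the chart-based covariate.
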